### Study Population

The main cohort will include patients presenting with clinically diagnosed COVID-19 in primary care requiring assessment of risk of clinical deterioration.

### Eligibility Criteria and Consent

Patients 18 years old and older, being seen (any form of contact, including face-to-face or remote) in a primary care setting where COVID-19 cases are occurring and running either a practice-based triage system or a COVID-19 remote monitoring service such as National Health Service (NHS)111 COVID-19 Clinical Assessment Service (CCAS) or a local equivalent, are enrolled in the study.

Patients being seen in practices not using a compatible electronic record system or using a remote monitoring system that cannot provide an output that is at least mapped to the appropriate Systemized Nomenclature of Medicine (SNOMED) concepts are excluded.

Patients locally record as being willing and able to provide informed consent for data linkage either at a GP contact (entered on a template) or as part of a “platform service” (checked by the patient on a template or via chatbot). If consent to data linkage cannot be obtained, an opt out will be provided and linkage sought under the Control of Patient Information provisions [8].

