### Study Objectives

The primary objective of the study is the development of a data-driven risk tool (RECAP-V1) for use in general practitioner (GP)-patient consultations (mainly by phone or video) in the context of COVID-19. As a secondary objective, the early warning risk tool will be externally validated on an independent dataset. As a third objective, the performance of the model in additional datasets will be assessed. Data for both model development and model validation will be prospectively collected.

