#### Missing Data

The extent of missing data for each variable (outcome and predictors) will be assessed among all patients. Particular note will be taken of the potential for missing data in the oxygen saturation and temperature fields (in case the patient does not have instruments to measure these), and for respiratory rate (difficult to estimate unless independently counted visually) as these are considered particularly important factors for outcome.

If model outcome data are missing for >5% of the patients, methods to deal with missing data will be used and a sensitivity analysis to estimate the effect of using these methods will be carried out by comparing the estimated risk obtained without implementing a missing data method and the risk estimated using missing data methods.

The degree of missingness in predictor variables will be assessed. If the degree of missingness is above 50% for any predictor variable, then that predictor variable will be excluded from the model. If the degree of missingness is less than 50%, the data will be imputed using multiple imputation chain equations [18]. A total of 5 imputations will be performed and aggregated based on Rubin’s rules [19].

Data missingness mechanisms will be investigated to ascertain if the data are missing completely at random, at random, or not at random. This will be performed by considering the data structure to understand the dependency relationships between the missing data and the observed data. The missing data will then be described in relation to the degrees of missingness, missing data patterns, and possible reasons for missingness. We will also compare the characteristics of the patients with missing data and patients with complete data entries, which will allow us to assess the plausibility of the data missing completely at random. The distributions of the continuous predictor variables will be investigated for normality. Any missing continuous data that are not distributed normally will be transformed to a normal distribution for imputation and transformed back to the original scale for the final analysis.

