Multiple imputation chain equations [18,20] will be used, and all of the predictor variables (with less than 50% missing data) will be included in the imputation model. Variables without missing data will also be included, and the outcome variable (hospital admission) will be used for imputation of the predictor variables. We will use linear regression for continuous variables (normally distributed or transformed), and logit or ordinal logit regression for categorical variables. We will compare observed and imputed values, especially for variables for which the fraction of missing data is large [21].

The same imputation methods will be used in all datasets, for both continuous and categorical variables.

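### Contact mode probably drives missing respiratory rate, but it is named neither in the imputation model nor in the performance breakdown; the direction and size of any mis-calibration are open

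*SAP article*

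**What the plan says.** Eligibility Criteria and Consent takes patients "being seen (any form of contact, including face-to-face or remote) in a primary care setting". Under Definition of Analysis Population, the primary model is built on iCare and validated on the RSC Practice network, with no split by contact mode in either.

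Study Objectives describes the tool as "for use in general practitioner (GP)-patient consultations (mainly by phone or video) in the context of COVID-19".

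Missing Data singles out oxygen saturation and temperature, which need instruments the patient may lack, and adds a note "for respiratory rate (difficult to estimate unless independently counted visually) as these are considered particularly important factors for outcome". It has two rules that matter here:

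- On dropping a predictor: "If the degree of missingness is above 50% for any predictor variable, then that predictor variable will be excluded from the model".
- On the imputation model: "all of the predictor variables (with less than 50% missing data) will be included in the imputation model". It continues: "Variables without missing data will also be included, and the outcome variable (hospital admission) will be used for imputation of the predictor variables".

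The text of Model Predictor Variables does not list contact mode. (Figure 1 could not be read here; if it lists contact mode, the imputation part of this point falls.) Model Internal Validation and Evaluation and Subgroup Analysis examine performance by age and gender only.

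**The concern.** The plan identifies a likely cause of missingness and then does not use it. A phone contact gives no view of the patient, whereas a video or face-to-face contact does. Respiratory rate is therefore likely to be missing far more often for some modes than for others.

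Multiple imputation by chained equations relies on the data being missing at random given what is in the imputation model. Suppose patients assessed in different ways also differ in respiratory rate, beyond what the other predictors and the outcome explain. Leaving mode out then breaks that assumption for a reason the consultation record could supply. The imputed rates are shifted, and the fitted equation attaches the wrong risk to a given rate.

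The plan regards respiratory rate as particularly important, and it enters all three planned interaction tests. Remote contacts are the main setting of use, yet no planned output shows how the model performs in them.

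**Working it through.** The plan gives no figure on this point, so there is none to reproduce. It also gives no share of face-to-face contacts, no completeness by mode and no difference in respiratory rate by mode. **Every mode-specific input below is an assumption.** The simulation shows what can happen, not what will.

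**Set-up.** 400,000 patients per scenario. Age A and respiratory rate R are in SD units, with correlation 0.3.

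- Contact mode: logit P(face-to-face) = g × R, so about half are face-to-face. With g = 0.5 or 1.0 the odds rise e^0.5 = 1.6-fold or e^1.0 = 2.7-fold per SD.
- Missing R: 80% of remote and 5% of face-to-face contacts.
- Admission: logit P = −2.75 + 0.5A + 0.6R.
- R is imputed five times by linear regression on A and the outcome, with or without mode. The logistic model is then refitted.
- O/E = observed admissions / sum of predicted risks, in remote patients.

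**Does the variable survive the 50% rule?** Overall missingness = (1 − p) × 0.80 + p × 0.05, where p is the face-to-face share. At p = 0.5 this is 0.400 + 0.025 = 0.425, so R is kept and imputed. It stays below 0.50 only if 0.80 − 0.75p < 0.50, that is p > 0.40. At p = 0.2 it is 0.64 + 0.01 = 0.65, so R is dropped and the imputation problem does not arise.

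**Results with mode left out, true R entered when predicting.**

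- Face-to-face patients have higher R: imputed rates 0.32 SD too high (g = 0.5) or 0.57 SD too high (g = 1.0); O/E 1.08 or 1.13, i.e. under-prediction.
- No difference (g = 0): O/E 1.00.
- Face-to-face patients have lower R (g = −0.5, −1.0): O/E 0.93 or 0.88, i.e. over-prediction.
- Milder missingness (about 30% face-to-face, 60% missing remotely), face-to-face higher: O/E 1.04 to 1.09.

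**The same fitted models scored on imputed R.** With face-to-face patients higher, predicted/observed is 1.08 or 1.18, i.e. O/E of about 1/1.08 = 0.93 or 1/1.18 = 0.85. The sign is opposite to that on true values. Inflated rates attached to patients with few admissions make the equation assign too little risk to a given rate. Entering the true, lower rate then predicts too little; entering the inflated imputed rate predicts too much.

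**With mode added to the imputation model.** The error in imputed R is at most 0.01 SD and O/E is 0.99 to 1.01 in every scenario above.

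**If mode affects admission in its own right.** With an assumed log-odds of +0.5 for face-to-face and g = 1.0, O/E on true values is 0.86 without mode in the imputation model and 0.78 with it. Imputation alone does not cure that.

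**A second specification** used 25–40% face-to-face, R recorded in 90% of face-to-face and 35–40% of remote contacts, and differences of −3 to +3 breaths/min, scored on imputed values. It gave predicted/observed from 0.95 to 1.10 in remote patients without mode, and 1.00 to 1.01 with it.

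**The case against.** A reader might infer that remote patients receive values from sicker patients seen in person and that their risk is therefore under-predicted. The documents do not support that. Nothing says that patients seen in person have higher respiratory rates. The sign changes with the direction of the difference, with scoring on true or imputed values, and with any direct effect of mode on admission. Nor are values borrowed only from in-person patients: video allows visual counting, remote patients with a recorded rate also contribute, and imputation is conditional on the other variables.

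The plan also has safeguards. It will investigate missingness mechanisms and compare patients with and without missing data. Complete variables enter the imputation model, which could admit contact mode. Heavy missingness triggers exclusion. Models without respiratory rate, temperature and saturation are planned, and shortness of breath can replace respiratory rate in the interaction tests. The other retained predictors, such as breathlessness trajectory, saturation and heart rate, should absorb part of any difference by mode; the simulations condition on less and may overstate the effect. CCAS and DoctalyHealth have separate models, so the primary model does not pool those services. A condensed article may also leave out a full list of auxiliary variables.

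Most of this stands, and it limits the claim. It does not remove it. The missingness comparison has no stated consequence for the imputation model, the models without respiratory rate are exploratory, and the provision for complete variables does not name mode. The article does specify the content of the imputation model and the performance subgroups, and mode is in neither. Because the same imputation applies in all datasets, external validation scored on mode-blind imputed values could show an error of the opposite sign to that met in use.

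**Conclusion.** The point holds in conditional form. The plan pools contact modes, ties the recording of an important predictor to how the patient is assessed, and names mode neither for imputation nor for reporting performance. Mis-calibration follows only if respiratory rate differs by mode given the other predictors and the outcome, and if the variable stays under 50% missing. The illustrative range is O/E of about 0.9 to 1.13 in remote patients on true values, and 1.00 with no difference. Both ends rest on assumed inputs, and the documents do not settle direction or size. This is a modest, inexpensive improvement, not a demonstrated bias.

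A remote-only headline validation would go further than the plan's wording requires. Its stated use is mainly, not solely, remote, and its second research question concerns primary care assessment generally. The RSC sample stood at 1303 on May 10, 2021, against a target of 1400.

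**What to change.** 1. In Missing Data, name contact mode (phone, video, face-to-face) as an auxiliary variable in the imputation model, in every dataset where the consultation record holds it and it varies. That the field can be extracted is an assumption to confirm first.
2. In Objective 2, report calibration, sensitivity and specificity in the RSC data separately for remote and face-to-face contacts, alongside the all-contacts estimate. Calibration needs stating because that section lists only specificity, sensitivity and the predictive values.

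The second change is needed even if the first is made, because imputation cannot correct a direct effect of mode on admission.

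The cost is one extra field, one sentence in each section, and wider intervals by mode. At the plan's 10% admission rate, 1303 patients give about 1303 × 0.10 = 130 admissions to divide between the modes, so the by-mode sensitivity will be imprecise and should be presented with its interval.

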### Population Data

The data are collected in four different systems: (1) iCare (North West London Whole Systems Integrated Care), which is the Imperial analytics platform for high-paced processing of patient data from North West London practices; (2) the Royal College of General Practitioners (RCGP) Research and Surveillance network (RSC Practice network), which is a general practice sentinel network that collects data from practices across England and Wales; (3) NHS111 CCAS; and (4) DoctalyHealth Care, a home monitoring service for patients with a diagnosis of COVID-19.

The data will be collected using templates embedded in health record systems used in routine contacts for patients with suspected COVID-19, and then the records will be linked between primary and secondary care. The consent for this data linkage will also be collected. Once recruited, patients will be followed up for 28 days after the COVID-19 diagnosis.

### Definition of Analysis Population

The primary population set is patients presenting with clinically diagnosed COVID-19 in general practices and requiring assessment for the risk of clinical deterioration. The primary RECAP-V1 model will be built using data from iCare and externally validated using data from the RSC Practice network.

Additional population sets are patients that are part of DoctalyHealth, as well as patients who are being assessed by the NHS111 CCAS. Based on clinical expertise, the patients who are being assessed as part of NHS111 CCAS are expected to be experiencing more severe symptoms of COVID-19. Similarly, for DoctalyHealth, the data are collected from a home monitoring system; hence, we are expecting this patient population to be different from the iCare and RSC Practice network populations. Moreover, some of the important clinical parameters such as oxygen saturation or rate of breathing may be missing for DoctalyHealth.

A separate RECAP model will be built for the CCAS patients and the DoctalyHealth patients.

### Model Outcome Variable

The outcome variable considered in building the risk model RECAP-V1 is hospitalization within 28 days following a positive ascertained diagnosis of COVID-19 (either a clinical diagnosis or a polymerase chain reaction test).

Hospitalization is defined as a patient being admitted and having spent at least one night in a bed in a hospital in the period following a COVID-19 diagnosis and up to 28 days following the diagnosis.

### Model Predictor Variables

The predictor variables to be included as candidates for the model have been decided through a Delphi process by the investigators and the research team, which are presented in Figure 1. The SNOMED codes are also outlined for these predictors. These predictor variables are contained in RECAP V0 [9], which include patients’ sociodemographic information (eg, age, ethnicity, adverse social circumstances) and comorbidities. The predictors that will be included in the primary model are continuous (heart rate, respiratory rate, trajectory of breathlessness, oxygen saturation at rest, oxygen saturation after 40 steps, temperature, time from first symptom [days], age, BMI) and categorical variables (profound tiredness or fatigue, muscle aches, myalgia, cognitive decline, being on a COVID-19 shielded list [10], gender, ethnicity, diabetes, hypertension, coronary heart disease, chronic kidney disease, and adverse social circumstance).

**Figure 1 figure1:**
[figure not shown]
RECAP-V1 model predictor variables and their clinical severity, adapted from Greenhalgh et al [11]. O/E: on examination; ORCHID: Oxford-Royal College of General Practitioners Clinical Informatics Digital Hub; RECAP: Remote COVID-19 Assessment in Primary Care; SNOMED: Systemized Nomenclature of Medicine.

### Statistical Methods

#### Baseline Demographics

Patient characteristics will be summarized. Summaries of continuous variables will be presented as means (SD) if normally distributed and as medians (IQR) for skewed data; categorical variables will be presented as frequencies and percentages. Baseline demographics will include all of the RECAP V0 variables outlined in Figure 1.

#### Objective 1 (Primary Objective): Development, Internal Validation, and Identification of Clinical Cut-Off Points of the RECAP-V1 Model

The primary objective of the study is to develop a predictive model based on a logistic regression of the predictive parameters using data from the iCare system. The model will be internally validated by bootstrapping the dataset. Following the internal validation, two cut-off points will be used as separators for red, amber, and green risk of a particular outcome with associated interval likelihood ratios (LRs).

A probabilistic risk prediction based on a multivariable logistic regression model, including the variables in Figure 1 as factors, will be performed on the patients from the iCare dataset, with continuous predictors being treated as fractional polynomials to reflect the potential nonlinearity of the variables. The model will allow estimation of the likelihood of a particular patient being admitted to hospital within 28 days of a COVID-19 diagnosis (primary patient outcome). Some of the variables will be checked for independence from each other by including interaction terms in the model. We will test interactions between BMI and respiratory rate (or shortness of breath if respiratory rate is not collected), age and respiratory rate (or shortness of breath), and coronary heart disease and respiratory rate (or shortness of breath).

The significance of each factor in the list of predictor parameters from Figure 1 will be investigated using a backward elimination regression model, where a multivariable regression model is constructed in the first instance including all of the parameters from the list in Figure 1 and their performance assessed to check for significance. Subsequently, a model using only the predictor factors that were found to be statistically significant (*P*<.05) for the prediction of results will be run.

The final model will then be used to estimate the predicted risk for each patient in the iCare dataset. Based on this continuous risk, the specificity and the sensitivity will be calculated based on the formulas shown in Figure 2. All analyses will be completed after the last patient’s final follow-up.

**Figure 2 figure2:**
[figure not shown]
Sensitivity and specificity calculations based on test risk prediction and the real outcome, along with the positive and negative predictive value formulas. NPV: Negative Predictive Value; PPV: Positive Predictive Value.

#### Model Internal Validation and Evaluation

The model will be validated internally by bootstrapping to ensure it performs well. The goodness of fit of the model will be assessed using the area under the receiver operating characteristic (ROC) curve and optimism-corrected smoothed calibration curves [12] to determine the performance of the model in predicting outcomes in the bootstrapped cohorts, with the final relationship between the predicted and the observed data being expressed as the McFadden R^2^ value [13].

To provide better representation of model fit, calibration and discrimination will be performed to better evaluate the accuracy of the model. Calibration of the model will be achieved using Loess-smoothed calibration plots as described above. For the purpose of analyzing discrimination, the data will be stratified by age (65 years old as a cut-off point) and gender. Hence, the model will be tested in population subgroups with age and gender for the subgroup definition. Brier scores will be used to measure the accuracy of the predictions of the model [14].

For each patient in this set, the result of the RECAP-V1 model will be calculated, and an ROC curve will be plotted from the highest to lowest values to determine the cut-off points for the predicted risk that optimize the specificity and sensitivity of the predictor model for red, amber, and green risk groups. The risk groups represent the relative risk of a particular patient outcome, with green signifying a very low risk, amber being a moderate to high risk, and red being a very high risk. This stratification ensures that there is a minimal number of false negatives in the final model and patients are not considered to be at low risk unless absolutely certain. The rate of increase and the point of inflection for the ROC curve will be used to inform the two cut-off points at the green/amber and amber/red points, which will be used as thresholds. The choice of optimum cut-off points is a clinical decision based on the shape of the resulting ROC curve (eg, how well-behaved the curve is, whether it is asymmetrical). Cut-off points should be clinically informative (ie, have a gradient representing the interval LR that is either greater than 2 or less than 0.5 so that the score changes the prior probability sufficiently). With a two cut-off point score for the red/amber/green (admit/monitor/advise) categories, the red/amber cut-off point should be in the steepest part of the curve (the most abnormal scores) where the LR will increase the risk of admission, and the amber/green cut-off point should be in the shallow part of the curve (the least abnormal scores) where the LR will decrease risk of admission. The ROC curve will thus be divided into three parts from the most abnormal to the least abnormal with three associated interval LRs; we will aim to allocate scores based on maximizing the “most abnormal” interval LR and minimizing the “least abnormal” interval LR with the middle interval LR likely to be around 1. There are several statistical tools for finding these points; however, in our opinion, selecting appropriate points from inspection of the ROC has the highest clinical validity [15].

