### Sample Size

#### Model Development and Internal Validation

Assuming that 10% of patients diagnosed with COVID-19 will be admitted to hospital [6], a 0.05 acceptable difference in apparent and adjusted Cox-Snell R-squared, 0.05 margin of error in estimation of the intercept, a binary outcome based on admission to hospital, and a maximum of 24 predictor parameters [5], we estimate that the minimum sample size required for new model development is 1317 participants enrolled for the development set [7].

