## Results

A total of 173 active primary care practices have enrolled for the recruitment of patients across the iCare and RSC practice network. As of May 10, 2021, the study has recruited a combined sample of 3732 participants for the development, validation, and accuracy assessment of the model. A total of 2429 participants have been recruited from North West London GP practices (iCare), including the primary care data on the patients’ signs and symptoms during the full 28-day follow-up period; 1303 patients have been recruited from RSC practices, similarly recording the signs and symptoms of patients over the full 28-day follow-up period.

Through the DoctalyHealth platform, data have been collected using a remote monitoring system to record the patients’ clinical parameters, as well as signs and symptoms. The dataset comprises approximately 5000 patients and will be used to develop a model for this patient set. Additionally, 2088 patients have been recruited through NHS111 CCAS.

The final results of the model development and validation will be reported following the TRIPOD guideline [28] for prediction model development and validation. This study is expected to conclude in December 2021.

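### The bootstrap measures overfitting, but no step applies it to the RECAP-V1 equation, so the stated admission risks are expected to be somewhat too extreme

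*SAP article*

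**What the plan says.** All places are in the SAP article.

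- **Objective 1.** A logistic model with fractional polynomials for the continuous predictors and three tested interactions is reduced by backward elimination and rerun with the P<.05 factors only. Then: "The final model will then be used to estimate the predicted risk for each patient in the iCare dataset".
- **Model Internal Validation and Evaluation.** The bootstrap is used to assess the AUC and smoothed calibration curves corrected for optimism. Calibration and discrimination are introduced as ways to evaluate accuracy, followed by "Calibration of the model will be achieved using Loess-smoothed calibration plots as described above". Brier scores are also planned.
- **Objective 2.** External validation in the RSC data covers specificity, sensitivity, and negative and positive predictive value. No calibration measure is listed.
- **Sample Size.** The inputs are "Assuming that 10% of patients diagnosed with COVID-19 will be admitted to hospital", "a 0.05 acceptable difference in apparent and adjusted Cox-Snell R-squared", "0.05 margin of error in estimation of the intercept" and "a maximum of 24 predictor parameters". The result is that "the minimum sample size required for new model development is 1317 participants enrolled for the development set".
- **Results.** "A total of 2429 participants have been recruited from North West London GP practices (iCare").

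No section mentions a shrinkage factor, penalised estimation, an update of slope or intercept, or what to do if the calibration curve leaves the diagonal. The Introduction presents the article as the prespecified plan (Version 1.0) that sets out every step of development and validation.

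**The concern.** A calibration plot shows miscalibration; it does not remove it. Coefficients fitted by maximum likelihood after significance-based selection are on average too large in absolute value. In new patients, high predicted risks then tend to be too high and low ones too low. The bootstrap yields the quantity needed to correct this, the calibration slope, but the plan does not use it.

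What is at stake is the absolute risk. Objective 1 offers an individual patient's probability of admission within 28 days, and the Discussion describes the score as a measure of current hospitalization risk. Because external validation checks no calibration, an overstatement left after development would not be seen there either.

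**Working it through.** **1. Reproduce 1317.** The usual criterion for a target shrinkage S is n = P / [(S − 1) ln(1 − R²/S)], with P candidate parameters and R² the anticipated Cox-Snell R-squared. With P = 24 (stated), S = 0.90 and R² = 0.15 (both assumed; neither is stated): 24 / (0.10 × 0.18232) = 1316.4, rounded up to 1317.

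The two stated criteria give smaller numbers:
- R-squared difference of 0.05, at R² = 0.15. Scaled by the maximum Cox-Snell value at 10% events (0.478), S = 0.15/(0.15 + 0.05 × 0.478) = 0.863 and n = 915. Taken literally on the Cox-Snell scale, S = 0.15/0.20 = 0.75 and n = 431.
- Intercept margin of 0.05: (1.96/0.05)² × 0.10 × 0.90 = 138.3, so 139.

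The figure 1317 is thus matched exactly by a criterion that accepts an expected shrinkage of 0.90. That this was the route is an inference.

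**2. Expected shrinkage by the same formula, solved for S.** The lower R² of 0.072 is an assumed 15% of the maximum 0.478. The listed predictors (9 continuous, 12 categorical) and 3 interactions already make 24. Fractional polynomials for 9 continuous predictors add 9 to 27, giving about 33 to 51; this count is mine.

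| n | P | R² = 0.15 | R² = 0.072 |
|---|---|---|---|
| 1317 | 24 | 0.90 | 0.80 |
| 2429 | 24 | 0.94 | 0.88 |
| 2429 | 33 | 0.92 | 0.85 |
| 2429 | 51 | 0.89 | 0.78 |

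**3. What a factor does to one stated risk.** logit(p′) = c + S[logit(p) − c], with c = logit(0.06) = −2.752 (assumed typical risk of 6%). For S = 0.90 and p = 50%: −2.752 + 0.90 × 2.752 = −0.275, so 43%. For p = 30%, 26%. With S = 0.95, 50% becomes 47%.

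**4. Simulation of the selected model.** 10% events, backward elimination at P<.05, independent normal predictors, 12 true effects (assumed), 40 data sets per row, each judged in 20,000 new patients.

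| n | P | R² | Mean slope | Top 5%: stated v true | Gap (points) | Slope <1 |
|---|---|---|---|---|---|---|
| 2429 | 24 | 0.072 | 0.91 | 38.1% v 34.7% | 3.4 | 92.5% |
| 2429 | 24 | 0.15 | 0.95 | 56.3% v 53.9% | 2.4 | 80% |
| 2429 | 36 | 0.072 | 0.87 | 39.2% v 34.5% | 4.7 | 95% |
| 2429 | 36 | 0.15 | 0.90 | 58.4% v 53.8% | 4.6 | 97.5% |
| 2429 | 51 | 0.072 | 0.88 | 38.0% v 34.1% | 3.9 | 97.5% |
| 2429 | 51 | 0.15 | 0.92 | 57.0% v 53.4% | 3.6 | 92.5% |
| 1317 | 24 | 0.072 | 0.85 | 39.5% v 33.9% | 5.6 | 95% |
| 1317 | 24 | 0.15 | 0.90 | 56.7% v 52.1% | 4.6 | 90% |
| 1317 | 36 | 0.072 | 0.78 | 39.4% v 31.6% | 7.8 | 100% |
| 1317 | 36 | 0.15 | 0.87 | 58.9% v 52.7% | 6.2 | 95% |
| 1317 | 51 | 0.072 | 0.77 | 39.8% v 31.4% | 8.4 | 100% |
| 1317 | 51 | 0.15 | 0.86 | 59.0% v 52.4% | 6.6 | 95% |

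A separate simulation at n = 2429 (R² about 0.08 to 0.16, 24 to 40 parameters) gave slopes of 0.84 to 0.95 and gaps of about 2 to 6 points.

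**5. Effect of the correction at n = 2429.** In that separate simulation, multiplying by the bootstrap slope with selection repeated in each resample brought the mean slope to 1.00 to 1.02. It lowered the mean squared error of the stated risks in 68% to 84% of data sets. In a smaller run (25 data sets), the bootstrap slope without repeated selection was 0.94 to 0.96 against a true 0.90 to 0.95, so it corrected too little. With selection repeated and 40 to 54 parameters it was 0.84 to 0.85 against 0.90 to 0.91, so it corrected somewhat too much (0.90/0.85 = 1.06 to 0.91/0.84 = 1.08).

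**The case against.** Several points on the other side stand.

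- A reader might infer that the authors take a plot to be a recalibration. The preceding sentence in the same section speaks of evaluation, so *achieved* is loose wording for assessment. The fault is the missing correction step.
- A reader might infer that RECAP-V1 is bound to be overfitted. At 2429 patients the slope was at or above 1 in up to 20% of simulated data sets, so this is an expectation only.
- A reader might infer that the traffic-light groups are wrong. A uniform factor keeps the order of patients. With cut-offs carried through the same transformation, the groups, sensitivity, specificity, predictive values and interval likelihood ratios are identical before and after. This is the main deliverable, so the harm is limited to the quoted probabilities and the Brier score.
- The size depends on inputs the article does not give. One run at 2429 patients, with 54 parameters and a different effect pattern, gave 45% stated against 37% true. With 12 true effects at those settings the gap was about 3 to 4 points, so I do not rely on the larger figure. The minimum of 1317 has been exceeded by 84% (2429/1317 = 1.84).
- At the low end the error is small: in the lower half of patients, 1.8% stated against 1.9% true (24 parameters) and 3.2% against 3.6% (54).
- A reader might also hold that reporting McFadden R-squared leaves the 0.05 Cox-Snell limit unchecked. That limit is a sizing input, not a promised check, and one measure converts to the other once the event rate is known. It is at most a reporting note.

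The reply that a fuller plan may cover shrinkage is weak, because the article claims to set out all the analysis steps.

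**Conclusion.** The point holds as a missing step. The plan measures optimism, uses the P<.05-selected maximum-likelihood model unchanged for individual risks, and checks no calibration in the external data. Stated risks are expected, though not certain, to be too extreme. In the top 5% of patients the excess is about 2 to 6 percentage points at the recruited 2429 and about 4 to 8 points at the planned minimum of 1317 (4.6 to 8.4 in the table).

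These sizes are simulated. They rest on an assumed Cox-Snell R-squared of about 0.07 to 0.16, 24 to 51 candidate parameters, 10% admissions and an assumed pattern of effects. At the 24 parameters that the plan budgets and the recruited sample, the gap is 2.4 to 3.4 points. It is a worthwhile correction of moderate importance that leaves the risk groups intact.

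**What to change.** In Model Internal Validation and Evaluation, state that:

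1. each bootstrap sample repeats the whole model-building process: imputation, fractional polynomial selection and backward elimination;
2. the mean calibration slope across resamples is the uniform shrinkage factor;
3. the final coefficients are multiplied by this factor and the intercept is re-estimated;
4. this equation is frozen before cut-offs are derived and before the RSC validation, and the factor is reported.

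In Objective 2, add calibration slope and intercept in the RSC data, so that any remaining under- or over-correction is seen. Reword the quoted calibration sentence to say that the plots assess calibration.

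Cost: SAP wording, and somewhat more computing and programming than a bootstrap of the final model alone, because imputation and selection are repeated. Stated risks become slightly less extreme. If the slope is close to 1, the correction changes almost nothing.
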